## Abstract

**Background:**

Social jetlag is a chronic disruption of sleep timing that is characterized by different sleep timing during workdays and free days. Social jetlag has been associated with disturbed glucose metabolism, insulin resistance, and increased risk of metabolic syndrome and type 2 diabetes. In this study, we aim to investigate whether a combination of bright light therapy in the morning, bright light reduction in the evening and sleep advance instructions for 3 weeks reduces social jetlag and if this results in improvement of glycemic and metabolic control, sleep, mood and quality of life after 3 and 12 weeks in people with prediabetes and type 2 diabetes and to assess possible mediators, compared to regular sleep habits.

**Methods:**

In this randomized controlled trial, 60 people with prediabetes or type 2 diabetes with > 1 h social jetlag will be recruited. The intervention consists of bright light therapy (5000 lx) emitted by Vitamine-L (Lumie, UK) for 30 min each morning, combined with the advice to follow sleep advance instructions and to wear bright light-dimming goggles every evening for a period of 3 weeks. The control group adheres to their regular sleep habits and conditions. The primary outcome is glycated hemoglobin (HbA1c) after 12 weeks comparing the intervention and control in an intention-to-treat analysis. Secondary outcomes at 3 and 12 weeks are (1) social jetlag; (2) insulin sensitivity, fasting blood glucose, glucose-lowering medication use, and frequency of perceived hypoglycemia; (3) metabolic outcomes, including body mass index (BMI), waist circumference, body fat percentage, and blood pressure; (4) mood, including depression, fatigue and anxiety (measured with questionnaires); and (5) quality of life measured using EQ5D questionnaire. To assess other factors that might play a role as possible mediators, we will measure (para)sympathetic nervous system activity assessed with ECGs and electrochemical skin conductance tests, sleep quality and sleep phase distribution assessed with a sleep measuring headband (ZMax), the Dim Light Melatonin Onset in saliva samples (in a subgroup) at 3 and 12 weeks, the feeling of satiety and satiation with a 10-cm visual analog scale (VAS), diet using a food frequency questionnaire, and physical activity using an accelerometer (ActiGraph).

**Discussion:**

Social jetlag can contribute to poorer glycemic control and metabolic control in those with type 2 diabetes. With this intervention, we aim to reduce social jetlag and thereby improve glycemic and metabolic control. This could offer a way to improve overall population health and to reduce the disease burden of type 2 diabetes.

**Trial registration:**

ISRCTN registry ISRCTN11967109. Registered on 9 May 2024.

## Introduction

### Background and rationale {6a}

Social jetlag is a chronic disruption of sleep timing. It is caused by a discrepancy between biological rhythms and social engagements and is characterized by different sleep timing during workdays and free days [1]. Unlike sleep disruption caused by performing shift work or by traveling through different time zones, social jetlag is subtle but highly prevalent with estimates of over 70% in students and over 50% in the working population [2, 3]. Social jetlag usually starts during adolescence and remains present throughout the working career [1–4].

Social jetlag is associated with several pathologies such as mental health, cardiovascular disease, and type 2 diabetes [2]. In our recent meta-analysis, with data from 68 studies, we found that social jetlag is significantly associated with higher HbA1c levels, higher odds of obesity, and increased BMI [5]. In our cross-sectional study in people with type 2 diabetes, we showed that in working people, a high social jetlag was associated with a 1.87 mmol/mol (95% CI: 0.75 to 2.99) higher HbA1c and 5.81 mmHg (95% CI: 4.04 to 7.59) [6] higher blood pressure.

In other words, social jetlag can contribute to poorer glycemic and metabolic control in those with type 2 diabetes. As type 2 diabetes is a highly prevalent disease that causes a high burden of disease with over 400 million people affected worldwide [7], reducing social jetlag could offer a way to reduce this disease burden and improve overall population health.

Previous research has shown that it is possible to reduce social jetlag. For example, in the study by Geerdink et al. (2016) [8], 42 participants with > 1 h social jetlag were either exposed to a high-intensity blue light (intervention) or amber light exposure (placebo) in the morning for 9 days, combined with a sleep advancing scheme. This intervention advanced bed times by at least 45 min and wake-up times by at least 30 min, thereby changing the timing of sleep but not the duration, resulting in a reduction of social jetlag. Moreover, blue light was more effective in advancing the circadian clock, assessed through Dim Light Melatonin Onset (DLMO), compared to amber light in the placebo group and still had a significant effect 1 week after the intervention was stopped, with participants from the blue light group still waking up 30 min earlier. Overall, this study showed that blue light combined with a sleep advancing scheme for only 1 week is effective in reducing social jetlag [8].

The only other study assessing methods to reduce social jetlag was the study by Zerbini et al. (2018) [9]. For 2 weeks, they exposed 76 participants with at least 1.5 h social jetlag to either control (no intervention) or to blue light reduction in the evening condition. They showed a 36-min advance in sleep onset on workdays, but not on free days, an advanced DLMO, and a trend towards longer sleep in the intervention group compared to the control group, although social jetlag was not reduced [9].

Although it is possible to reduce social jetlag, currently there are no studies on the metabolic effects of these types of social jetlag reduction interventions. Therefore, our aim is to investigate whether a reduction in social jetlag for 3 weeks can improve glycemic and metabolic control, sleep, mood, and quality of life in people with prediabetes and type 2 diabetes.

### Objectives {7}

The primary objective of this study is to investigate whether a combination of bright light therapy in the morning, bright light reduction in the evening and sleep advance instructions for 3 weeks to reduce social jetlag results in an improvement of glycemic control in people with prediabetes and type 2 diabetes, compared to regular sleep habits. As a secondary objective, we assess the effect of the intervention on additional glycemic outcomes, metabolic control, sleep, mood, and quality of life.

### Trial design {8}

This study is a randomized controlled intervention study with two conditions. Stratified randomization allocates participants 1:1 to control or intervention conditions with equal distribution of sex, age, and social jetlag.

## Methods: participants, interventions, and outcomes

### Study setting {9}

Sixty participants with prediabetes and type 2 diabetes and > 1 h of social jetlag [10, 11] are recruited from our cohorts including the Hoorn Study [12] and the Hoorn Diabetes Care System Cohort [13]. We will recruit participants from these studies who previously consented to being (re)-approached for additional research. Participants will be invited to our clinical trial unit at the research center in Hoorn, which is part of the Amsterdam UMC.

### Eligibility criteria {10}

#### Inclusion criteria

Social jetlag (> 1 h) (calculated as the difference between midpoint of sleep during work days and free days)Prediabetes or type 2 diabetes: HbA1c > 39 mmol/mol (5.7%), fasting plasma glucose > 5.6 mmol/l, or 2-h OGTT > 7.8 mmol/l (according to the American Diabetes Association) or the use of any glucose-lowering medicationInformed consent (at inclusion for cohort study) to be contacted for future researchWilling to comply with the study procedures

#### Exclusion criteria

Having any other form of diabetes not considered type 2 diabetes (e.g., steroid-induced diabetes, diabetes type 3c, MODY, LADA).Excessive alcohol use (> 14 alcoholic consumptions per week)Having crossed more than 1 time zone in the month prior to participationWorking evening or shifts more than once per monthUnable to provide written informed consentVisually impaired (partial or total inability of visual perception)

### Who will take informed consent? {26a}

Written informed consent will be obtained and signed by the coordinating researcher or by a researcher/research nurse on their behalf before the start of any study-related assessments.

### Additional consent provisions for collection and use of participant data and biological specimens {26b}

Not applicable.

## Interventions

### Explanation for choice of comparators {6b}

For the control condition, participants will receive advice on healthy sleep habits and remain the same sleeping conditions and habits. Due to the nature and design of the study, blinding of the researchers or participants is not possible.

### Intervention description {11a}

The intervention condition is a combination of evidence-based techniques to realign social jetlag. It consists of three components: bright light therapy in the morning, sleep advance instructions, and bright light reduction in the evening.

First, for the bright light therapy, a Vitamin-L lamp (Lumie, UK) will be placed at 30 cm before the participant, yielding 5000 lx (https://www.lumie.com/products/vitamin-l), which is similar to outside light levels on a clouded day. The participant does not have to look straight into the light. Participants are requested to expose themselves to 30 min of bright light each morning by sitting in front of the lamp, while working on their computer or reading. Participants will receive a Vitamin-L lamp together with instructions for use. The Vitamin-L lamp is certified to ISO 13485 Medical Devices, QMS standard. Lights must pass rigorous safety tests and be supported by clinical research to meet the Medical Devices Directive EC93/42/EEC. They are approved for use for light therapy at home. Thus, in the present protocol, the lights will be used for the purpose they are designed for (i.e., administration of light). Due to recent insights about possible interactions of different photoreceptors in the non-visual effects of light [14], we believe that it is probably most efficient to use full spectrum bright light in the morning, rather than select a certain specific wavelength, such as blue light only.

Second, study participants are told to sleep more regularly, with similar sleep onset and sleep offset times on weekdays and weekend days. To support them with this, participants will follow a personal sleep-advancing scheme [8]. Based on self-report of the participant, the habitual sleep onset and habitual sleep offset will be calculated as the average of all days (week and weekend days). Then participants are asked to give their preferred sleep offset for all days of the week (similar for week and weekend days); preferred sleep onset is calculated as sleep offset − preferred sleep duration between 7 and 8 h. To advance sleep time with an average 20 min, the first 3 days, the light therapy will be scheduled 10 h after preferred sleep onset. On days 4–6, the light therapy is scheduled 9 h after preferred sleep onset and days 7–9 the light therapy 8 h after preferred sleep onset, if the earlier sleep onset is 3 h earlier. After the preferred sleep offset and onset are reached, the new schedule will be continued during the rest of the 3 weeks intervention.

As final part of the intervention, participants receive blue-light dimming goggles with instructions to wear them every evening from 18.00 h until they go to sleep [15]. When wearing the goggles they can still perform their usual activities, such as watching television or reading, with screens of electronic devices in dimmed modus [15, 16] as well as room lighting (dim lighting of the room, curtains closed).

### Criteria for discontinuing or modifying allocated interventions {11b}

Not applicable.

### Strategies to improve adherence to interventions {11c}

To improve adherence to the protocol and assess compliance, participants will send in a sleep diary of 7 days and wear an accelerometer (ActiGraph) as well as a light logger (Pendant Light 64 K Data Logger, HOBO CE) for 7 days after 1 week of the intervention program. The light logger is worn as pendant (2 by 3 cm) on a necklace outside the clothes, only taken off in water-based activities. The accelerometer and sleep diary will be used to assess adherence to the sleep schedule and the use of the light-dimming goggles, and the light logger will be used to assess compliance to the use of the bright light therapy. The control group receives no instructions and will continue with their usual sleep habits and conditions.

### Relevant concomitant care permitted or prohibited during the trial {11d}

There are no restrictions regarding concomitant care and medication use during this study.

### Provisions for post-trial care {30}

After the trial has finished, participants from the intervention group can keep adhering to their sleep instructions and can keep the blue light-dimming goggles. The Vitamin L lamp has to be returned. Also, participants from the control group can request a personal sleep schedule and blue light dimming goggles after the trial is finalized.

### Outcomes {12}

#### Primary outcomes

The primary outcome is HbA1c (mmol/mol) determined with turbidimetric inhibition immunoassay (Cobas c501, Roche Diagnostics, Mannheim, Germany) after 12 weeks.

#### Secondary outcomes

As secondary outcome measures, we will determine social jetlag measured using an adapted version of the Munich ChronoType Questionnaire (MCTQ) [10, 17] and sleep times from accelerometer data (ActiGraph) and EEG data from the sleep headband (ZMax) after 3 and 12 weeks. We will also determine other measures of glycemic control after 3 and 12 weeks. We will measure HOMA-IR determined from fasting insulin levels using an anti-body kit (AutoDELFIA Insulin kit; Wallac Oy), fasting blood glucose determined in fluorinated plasma with the UV test using hexokinase (Cobas c501, Roche Diagnostics); self-reported perceived hypoglycemia determined using a self-constructed questionnaire; and diabetes medication use assessed from the participants medication overview and described as type (ATC code), timing and dosage). Furthermore, we will measure metabolic parameters including anthropometrics (body weight, body fat percentage, and waist circumference); blood pressure (described as a continuous variable or dichotomous as hypertension, defined as systolic blood pressure and diastolic blood pressure ≥ 140/90 and/or use of hypertensive medication) Finally, mood, depression, fatigue, anxiety, and quality of life will be assessed using PROMIS questionnaires.

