## Statistical methods

### Statistical methods for primary and secondary outcomes {20a}f

Baseline characteristics will be described by the intervention arm as mean ± standard deviation (SD), as the median and interquartile range (if not normally distributed), or as numbers and percentages if categorical. Statistical analysis will be performed using RStudio version 4.3.0. We will conduct intention-to-treat analysis for primary and secondary outcomes using linear regression analysis, adjusting for baseline values. We will also adjust for the use of diabetes medication and perform sensitivity analyses on changes of medication use during the follow-up period of the study. Additionally, we will assess differences in intervention compliance and effect according to seasonality. Not normally distributed outcomes will be log transformed. We will assess effect modification by working status and chronotype. We will consider the chance of false positive findings when interpreting the results from testing our multiple secondary outcomes. If there is (despite randomization) an imbalance in participant characteristics, a sensitivity analysis will be conducted to assess the effect of the imbalance by adjusting for these variables.

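### The hypertension form of the blood pressure outcome requires both pressures to be raised in untreated participants and cannot register a fall while medication continues; the outcome should be fixed as continuous systolic and diastolic pressure

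*Protocol article*

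**What the plan says.** In the protocol article, Outcomes {12}, Secondary outcomes, blood pressure is listed among the metabolic parameters and may be "described as a continuous variable or dichotomous as hypertension". Hypertension is then "defined as systolic blood pressure and diastolic blood pressure ≥ 140/90 and/or use of hypertensive medication". No other section defines hypertension or says that one raised pressure is enough.

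Four other places bear on the point:

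- The Abstract (Methods) lists blood pressure among the metabolic outcomes at 3 and 12 weeks and does not mention hypertension.
- Background and rationale {6a} motivates the outcome by a difference of 5.81 mmHg (95% CI 4.04 to 7.59) associated with high social jetlag.
- Statistical methods {20a} analyses primary and secondary outcomes "using linear regression analysis, adjusting for baseline values". It names no model for a binary outcome. On medication it says "We will also adjust for the use of diabetes medication" and adds sensitivity analyses for medication changes, without naming blood pressure drugs.
- Concomitant care {11d} says "There are no restrictions regarding concomitant care and medication use during this study".

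**The concern.** The definition has two parts, and each causes a difficulty when the result is used as an outcome.

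The pressure part joins systolic and diastolic with *and*. If it is programmed as written, an untreated participant with only one raised pressure is classed as normal.

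The medication part is sufficient alone. A treated participant is hypertensive at every visit while treatment continues, whatever the cuff shows. Starting a drug turns a participant hypertensive even if pressure falls. Stopping one can turn a participant normotensive without any fall. Since medication is unrestricted, both can happen during follow-up.

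The article also does not say which form of the outcome is to be reported. At stake is whether the blood pressure result measures what the rationale is about, a shift in mmHg, or a status that misclassifies some participants and is fixed for others.

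**Working it through.** **Plan's own figure.** There is none to reproduce: the article gives no mean, SD or correlation for blood pressure, no share of participants on blood pressure drugs, and no power for this outcome. The logical check needs only the text. The size needs assumptions, marked below.

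**Step 1. The rule as logic.** Hypertensive = (systolic ≥ 140 and diastolic ≥ 90) or on medication.

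| Participant | As written | If either pressure suffices |
|---|---|---|
| Untreated, 160/80 | no | yes |
| Untreated, 130/95 | no | yes |
| Untreated, 141/91 | yes | yes |
| Treated, 160/80 | yes | yes |
| Treated, 120/75 | yes | yes |

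The first two rows show the effect of *and*. The last two show that a treated participant can go from 160/80 to 120/75 with no change in status. Replacing *and* by *or* repairs only the first problem.

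**Step 2. Size among untreated people (assumed inputs).** Assume bivariate normal readings with SD 16 systolic and 10 diastolic, correlation r from 0.5 to 0.7, and means from 130/76 to 140/80. At mean 135/78:

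- P(systolic ≥ 140) = 1 − Φ((140 − 135)/16) = 1 − Φ(0.3125) = 0.377
- P(diastolic ≥ 90) = 1 − Φ((90 − 78)/10) = 1 − Φ(1.2) = 0.115
- P(both), from the bivariate normal = 0.083 (r = 0.5) or 0.100 (r = 0.7)
- P(either) = 0.377 + 0.115 − P(both) = 0.409 or 0.392

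| Mean (mmHg) | Both raised | Either raised | Missed, as share of either: 1 − both/either |
|---|---|---|---|
| 130/76 | 5.1–6.5% | 28.1–29.6% | 77–83% |
| 135/78 | 8.3–10.0% | 39.2–40.9% | 74–80% |
| 140/80 | 12.7–14.5% | 51.3–53.1% | 72–76% |

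The last column applies to untreated people only.

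**Step 3. Size among everyone classed as hypertensive.** Let t be the treated share. Treated participants are captured by the medication part under either rule, so

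share missed = (1 − t)(either − both) / [t + (1 − t) × either].

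At mean 135/78, with t = 0.5 (assumed) and 60 participants, 30 are treated. Of the 30 untreated:

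- r = 0.5: either 30 × 0.409 = 12.3, both 30 × 0.083 = 2.5, missed 9.8; 9.8/(30 + 12.3) = 23%
- r = 0.7: either 30 × 0.392 = 11.8, both 30 × 0.100 = 3.0, missed 8.8; 8.8/(30 + 11.8) = 21%

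The same formula at the same mean gives 36–39% with t = 0.3 and 11–12% with t = 0.7.

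**Step 4. The medication part (assumed inputs).** Suppose 40% of untreated controls and 20% of untreated intervention participants are hypertensive at follow-up, and treated participants stay hypertensive. The observed difference is (1 − t) × 20 points. Power, two-sided at 0.05 with n = 30 per group and no baseline adjustment, is approximately

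Φ{[Δ − 1.96 √(2p̄(1 − p̄)/n)] / √[(p₁(1 − p₁) + p₂(1 − p₂))/n]}.

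| Treated share t | Control vs intervention | Difference | Power |
|---|---|---|---|
| 0 | 40% vs 20% | 20 points | 39% |
| 0.3 | 58% vs 44% | 14 points | 19% |
| 0.5 | 70% vs 60% | 10 points | 12% |
| 0.7 | 82% vs 76% | 6 points | 8% |

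The 20-point contrast is chosen only to show the dilution. The article does not claim it.

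**Step 5. Which form the rest of the article supports.** The {6a} rationale is in mmHg, the Abstract names blood pressure and not hypertension, and {20a} names linear regression adjusted for baseline. All three match a continuous outcome.

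**The case against.** The best defence is that this is loose wording. Writing systolic and diastolic pressure next to 140/90 is common shorthand, *or* may have been intended, and the continuous form is listed first and is the one the analysis section suits. A dichotomy that is only described may never be tested. Counting treated people as hypertensive is also an ordinary way to classify status, and the rewording proposed below keeps it.

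Most of this stands and limits the point. It does not remove it: the text says *and*, uses *and/or* for medication a few words later, and offers the dichotomy as an alternative form of a listed outcome. Choosing the analysed form is often left to the analysis plan, but a definition that misclassifies when coded as printed is an error in the article itself.

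Some stronger readings are tempting and are not supported:

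- *The rule misses about three quarters of raised readings.* That holds only for untreated people under assumed distributions.
- *Raised systolic with normal diastolic pressure is the usual pattern in this population.* The article says nothing on this.
- *Treated participants cannot show improvement.* This applies only to the dichotomy, and only while medication continues. The continuous form registers their fall.
- *The reported form will be picked after seeing the data.* The article leaves the form open, but the named model points to the continuous one, and {17a} provides for a blinded analyst.

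**Conclusion.** The point holds as a minor one on a single secondary outcome. Two facts rest on the text alone: the literal definition requires both pressures to be raised in untreated participants, and it cannot register a fall in pressure in treated participants while medication continues. The dichotomy is therefore poorly suited to measuring an effect at 3 and 12 weeks, and the article's own model and rationale fit only the continuous form.

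The size is illustrative, because every blood pressure input and the treated share are assumptions. Under those in the working, about 5–15% of untreated people are flagged instead of 28–53%. The share missed among all who would be classed as hypertensive is about 21–23% at mean 135/78 with half treated, and it moves strongly with the treated share.

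A reader might infer that the trial's main conclusion is at risk. It is not: the primary outcome (HbA1c at 12 weeks), the sample size and eligibility do not use this definition.

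**What to change.** In Outcomes {12}, Secondary outcomes:

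1. State that the blood pressure secondary outcomes are systolic and diastolic pressure in mmHg, continuous, at 3 and 12 weeks, analysed with the baseline-adjusted linear regression already planned.
2. Reword the dichotomy as: *systolic ≥ 140 or diastolic ≥ 90 mmHg and/or use of antihypertensive medication*. This also corrects the printed term for the drugs ("and/or use of hypertensive medication").
3. Say that the dichotomy is used only to describe participants at baseline.

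The cost is a change of wording in one outcome definition. Blood pressure is already measured at baseline, 3 and 12 weeks, and medication use is already recorded, so no new data or visits are needed.
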